**Figure 2 clc24164-fig-0002:**
[figure not shown]
Ablation procedure details. (A, B) Posterior–anterior view of the voltage map (CARTO) during CS pacing after the PVI (A) and LAPWI (B) with a radiofrequency catheter in the same case. (C, D) Posterior–anterior view of the voltage map (EnsiteⅩ) during CS pacing after the PVI with a CB (C) and LAPWI with a radiofrequency catheter (D) in the same case. In each figure, the blue circles are depicted as the estimated positions of the CB, the ablation points are described as red‐colored tags, and the purple area indicates a voltage ≥0.5 mV. In the EnsiteⅩ voltage maps, the gray area indicates a voltage ≤0.1 mV, and in the CARTO voltage maps, the red area indicates a voltage ≤0.1 mV. The isolated area shown as that surrounded by the black line in each figure will be measured. CB, cryoballoon; CS, coronary sinus; LAPWI, left atrial posterior wall isolation; PVI, pulmonary vein isolation; RF, radiofrequency.

### Postablation management

2.5

All patients will receive a proton pump inhibitor for at least 1 month. Follow‐up visits will be required at 1, 3, 6, 9, 12, and 18 months after the ablation procedure in all patients, and they will undergo 12‐lead electrocardiograms at each visit (Figure 3). Routine 7‐day ambulatory electrocardiograms (7‐day Holter ECG) (Gram, Durantis Co. Ltd) will be performed at 6, 12, and 18 months after the procedure, and analyzed by the staff who are not involved with the study outcomes. The electrophysiologists will evaluate the clinical outcomes at every visit in person, and additional monitoring such as, 24 hours to 7 day Holter electrocardiograms, patient activated event recorders for 1 month (HCG 801, Omron), 7‐ to 14‐day autotriggered event recorders (SpiderFlash, ELA Medical), or commercially available photoplethysmography (Apple Watch, Apple Inc.) will be used if necessary.

**Figure 3 clc24164-fig-0003:**
[figure not shown]
CORNERSTONE AF trial flow chart. AADs, antiarrhythmic drugs; CT, computed tomography; ECG, electrocardiography; LAPWI, left atrial posterior wall isolation; MRI, magnetic resonance imaging; PAGI‐SYM, patient assessment of upper gastrointestinal symptom severity index; PVI, pulmonary vein isolation; TTE, trans‐thoracic echocardiography.

Antiarrhythmic drugs will be basically discontinued within 3 months after the procedure. Amiodarone use will not be permitted after the procedure. Trans‐thoracic echocardiography will be performed before the procedure and at 12 months after the procedure to assess the atrial remodeling and cardiac function. Cardiac enhanced computed tomography will also be considered before the procedure and at 6 months after the procedure, if the patients consent to receive it, to examine whether there will be PV stenosis. To evaluate the symptomatic gastric hypomotility, the patients will be required to report their symptoms through a 20‐question Patient Assessment of Upper Gastrointestinal Disorders‐Symptom Severity Index^16^ before the procedure, and 3–4 days and 1 month after the procedure. The responses to each question in this tool will be rated from 0 to 5, with a score of 5 indicating a severe symptom. Redo procedures will be allowed at any time after the initial ablation procedure according to the physicians' decision if patients suffer from any atrial arrhythmia recurrence, and the strategy of the procedure will be left to the operators' discretion. The durability of the PVI and LAPWI will be evaluated only in patients who undergo redo procedures.

### Sample size calculation

2.6

The sample size is based on the primary endpoint of this study, namely the atrial arrhythmia recurrence‐free rate at 18 months after a single procedure. Based on the previous literature,^2^, ^17^ we assume that 65% of PsAF/long‐PsAF patients will be free from atrial arrhythmia recurrence at 18 months after a PVI alone and that the atrial arrhythmia free rate will increase by 10% when an LAPWI is additionally performed. Moreover, we assume the possibility of a 10% dropout of participants. To reject the null hypothesis that the probability of the primary endpoint will be the same between the experimental and control subjects, with a power of 80% and a significant level of 5% (two‐sided), a total of 516 patients will be required with a randomization ratio of 1:1.

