**Methods:**

The CORNERSTONE AF study is a prospective, randomized, multicenter study investigating patients with AF persisting for >7 days and <3 years undergoing first‐time AF ablation. They will be randomized to pulmonary vein isolation (PVI) or PVI + LAPWI in a 1:1 manner. Although PVI can be performed with either radiofrequency catheters or cryoballoons, only radiofrequency catheters will be permitted to achieve LAPWIs. Additional focal ablation targeting non‐pulmonary vein triggers will be allowed. A total of 516 patients will be enrolled in 17 centers between August 2022 and February 2024 based on the calculation with 80% power, considering the assumption that 65% and 75% of the PVI and PVI + LAPWI group patients will be free from atrial arrhythmia recurrence 18‐months postprocedure (10% of dropout). The primary endpoint is freedom from documented atrial arrhythmias 18 months postsingle procedures. Clinical follow‐up will include 7‐day ambulatory electrocardiograms and routine outpatient consultations by electrophysiologists at 1, 3, 6, 9, 12, and 18 months postprocedure.

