### Statistical analysis

2.7

The full analysis set (FAS) for the primary efficacy analysis is defined as the set of all randomized patients who meet all inclusion criteria and its statistical evaluation is based on the intention‐to‐treat principle. An analysis of the per‐protocol set will be also be performed to assess the robustness of the results of the analysis using FAS. Continuous variables of the baseline patient characteristics will be expressed as the mean ± SD, or median with the interquartile range, and their distributions among the groups will be compared utilizing a Student *t* test or Mann‐Whitney *U* test. Categorical variables of the baseline patient characteristics will be reported as numbers and percentages, and their distributions among the groups will be compared with the *χ*
^2^ or Fisher exact tests. Missing data will not be imputed in these analyses.

The survival curves of the primary endpoint will be estimated using the Kaplan–Meier method and the difference in them between the additional LAPWI group and PVI alone group will be compared based on the log‐rank test. Patients not reported as having atrial arrhythmia recurrence events at 18 months and patients lost to follow‐up within 18 months will be censored at 18 months and the date they are last known to be free from any atrial arrhythmia recurrence, respectively.

No interim analyses will be conducted in this trial. A *p* < .05 will be considered to indicate statistical significance. A Cox regression analysis will also be utilized for the multivariate analysis regarding the freedom of atrial arrhythmia recurrence. For the secondary endpoints, the AF recurrence‐free rate and AT recurrence‐free rate will be analyzed with the same method as the primary endpoint. The AF burden reduction, total number of ablation sessions, and complication rate will be analyzed between the two groups by an appropriate statistical test according to the type of variables. There are no prespecified subanalyses.

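### 516 patients do not give 80% power for 65% versus 75%: with follow-up censored at 18 months the power is about 66–71%

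*Protocol article*

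**What the plan says.** Section 2.6 of the protocol article (Sample size calculation) sizes the trial on the recurrence-free rate at 18 months after one procedure. For the control arm, "we assume that 65% of PsAF/long‐PsAF patients will be free from atrial arrhythmia recurrence at 18 months after a PVI alone". The abstract shows that the assumed increase is absolute: "65% and 75% of the PVI and PVI + LAPWI group patients will be free from atrial arrhythmia recurrence". Section 2.6 sets 80% power and a two-sided 5% level, adds that "we assume the possibility of a 10% dropout of participants", and concludes that "a total of 516 patients will be required with a randomization ratio of 1:1". The abstract repeats the figure: "A total of 516 patients will be enrolled in 17 centers between August 2022 and February 2024".

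Section 2.7 (Statistical analysis) compares the arms by a log-rank test. It fixes the horizon: patients without recurrence, and patients lost earlier, "will be censored at 18 months and the date they are last known to be free from any atrial arrhythmia recurrence" respectively. Section 2.5 schedules the last visit at 18 months.

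**The concern.** All the inputs to a standard sample-size formula are stated, yet the total looks too small. A 10-point difference around 70% at two-sided 5% and 80% power normally needs well over 300 patients per arm before any dropout allowance. The plan has 258 per arm with the allowance already included.

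The 80% is the main design property claimed for the primary endpoint. If the true power is nearer two thirds, a non-significant result is much more likely than readers will be told, even if the assumed benefit is real. The Discussion already cites randomized trials that found no benefit of posterior wall isolation. A further non-significant result, presented as coming from a trial with 80% power, would carry more weight than it deserves.

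**Working it through.** **Inputs.** Section 2.6: control rate 0.65, 80% power, two-sided 5%, 10% dropout, 1:1, N = 516. Abstract: 0.75 in the experimental arm. Section 2.7: log-rank test, censoring at 18 months. Normal quantiles are 1.960 and 0.842; their sum squared is 7.849.

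**Attempt to reproduce 516: two proportions**
- Unpooled variance: n per arm = (0.65×0.35 + 0.75×0.25) × 7.849 / 0.10² = 0.415 × 784.9 = 325.7.
- Arcsine transformation: 327.6 per arm.
- Pooled variance: 328.5 per arm, or 329 rounded up.
- Total: 652–658. Divided by 0.9 for dropout: about 724–732. A continuity correction raises this to 776.

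**Attempt to reproduce 516: log-rank test**
- Hazard ratio = ln 0.75 / ln 0.65 = 0.668, so (ln HR)² = 0.1630.
- Events (Schoenfeld) = 4 × 7.849 / 0.1630 = 192.6.
- Average event probability at 18 months = (0.35 + 0.25)/2 = 0.30.
- N = 192.6 / 0.30 = 642. Divided by 0.9: 713 (715 if events are first rounded up to 193).
- Freedman's formula: 197.8 events, 659 patients, 733 after dropout (734 with rounding).

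No two-sided calculation with follow-up fixed at 18 months gives 516. Even with no dropout allowance, 516 falls short of the smallest answer, 642.

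**Power of 516 patients.** Power = Φ(√events × |ln HR| / 2 − 1.960), with |ln HR| = 0.4037.

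| Scenario | Events | Formula | Simulated log-rank |
|---|---|---|---|
| No dropout (516 informative) | 516 × 0.30 = 154.8 | Φ(2.512 − 1.960) = 70.9% | 70.8% |
| Exponential loss reaching 10% at 18 months | 516 × 0.2857 = 147.4 | 68.8% | 68.1–68.7% |
| Dropouts contribute nothing (464.4 informative) | 464.4 × 0.30 = 139.3 | Φ(2.383 − 1.960) = 66.4% | 66.0% (464 patients) |

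The pooled two-proportion formula gives 69.9% for 516 and 65.3% for 464 patients.

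**Effect detectable with 80% power.** Solving the same log-rank formula for the experimental rate gives 76.1% with 516 informative patients (HR 0.63) and 76.6% with 464.4 (HR 0.62), against 65% in controls.

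**Where 516 may come from.** The article gives no formula, so this is inference.
- *Survival calculation with a common closing date.* With 18 to 19 months of accrual, and every patient followed until 18 months after the last enrolment, the average event probability rises to 0.410–0.415. Then N = 192.6/0.410 = 470 to 192.6/0.415 = 464, or 522 to 515 after dropout. A related exponential-difference method (Lachin–Foulkes) with 18 + 18 months and exponential 10% loss gives 516.0.
- *One-sided 5% comparison of two proportions with no dropout allowance.* This gives 257–259 per arm.

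The first route counts recurrences up to about 36 months, which Section 2.7 censors. The second contradicts the two-sided level and the 10% dropout in Section 2.6.

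**The case against.** The strongest defence is that the sponsor probably used survival software with staggered entry, and that the full protocol, which is not shown, may state that follow-up model. Under such a model 516 is about right: simulated power with 18 months of accrual plus 18 months of further follow-up is 80.6% with exponential loss. But the analysis in the article discards every event after 18 months and the scheduled visits end there. If this is where the figure came from, the sample size relies on events that the primary analysis does not count.

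A second objection is that the survival figures rest on an assumed hazard shape. For the fixed-horizon log-rank calculation they need only proportional hazards: 65% versus 75% at 18 months then fixes both the hazard ratio and the 30% event fraction. The two-proportion result needs no hazard assumption and agrees.

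Three qualifications stand:
- The 71% is the no-dropout limit. Under the plan's own 10% dropout, power is about 66–69%.
- The origin of 516 is conjecture, and the finding does not depend on it.
- An article may omit the formula, and the test is already stated to be two-sided. Neither is a fault; the fault is a total that its own stated inputs do not support.

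**Conclusion.** The concern holds. The stated inputs require about 713–734 patients, roughly 200 more than planned. With 516 patients and censoring at 18 months, log-rank power for 65% versus 75% is 66.4% if dropouts contribute nothing, 68.8% with exponential 10% loss and 70.9% with no loss. The risk of missing the assumed benefit is thus 29–34% rather than 20%. The gap is far larger than rounding or the choice of formula can explain. Reading the 10% increase as relative does not help: the abstract gives 75%, and 71.5% would need far more patients (1,608 by two proportions before dropout).

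The result assumes the stated recurrence-free rates, proportional hazards for the log-rank figures, and dropout unrelated to recurrence.

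**What to change.** In Section 2.6 and the abstract, replace the 80% power claim. State that 516 patients, analysed by a two-sided 5% log-rank test with follow-up censored at 18 months and 10% dropout, give about 68% power (range 66–71% across dropout assumptions) for 65% versus 75%, or 80% power for about 65% versus 76.5%. Add one sentence on the follow-up assumption behind the number, so that it agrees with Section 2.7. This is a wording change with no extra patients; its cost is a less favourable power statement.

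If the sponsor prefers to keep 80% power for 65% versus 75%, the total must rise to about 713–734. Enrolment stood at 331 in August 2023 and was to continue to February 2024, so that choice would mean a longer or faster recruitment. Counting events after 18 months instead would change the primary analysis and would need follow-up beyond the current visit schedule.

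It would also help, though the correction does not depend on it, to report the 18-month difference and the hazard ratio with 95% confidence intervals, so that a non-significant result is not taken as evidence of no benefit.

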### Statistical analysis

2.7

The full analysis set (FAS) for the primary efficacy analysis is defined as the set of all randomized patients who meet all inclusion criteria and its statistical evaluation is based on the intention‐to‐treat principle. An analysis of the per‐protocol set will be also be performed to assess the robustness of the results of the analysis using FAS. Continuous variables of the baseline patient characteristics will be expressed as the mean ± SD, or median with the interquartile range, and their distributions among the groups will be compared utilizing a Student *t* test or Mann‐Whitney *U* test. Categorical variables of the baseline patient characteristics will be reported as numbers and percentages, and their distributions among the groups will be compared with the *χ*
^2^ or Fisher exact tests. Missing data will not be imputed in these analyses.

The survival curves of the primary endpoint will be estimated using the Kaplan–Meier method and the difference in them between the additional LAPWI group and PVI alone group will be compared based on the log‐rank test. Patients not reported as having atrial arrhythmia recurrence events at 18 months and patients lost to follow‐up within 18 months will be censored at 18 months and the date they are last known to be free from any atrial arrhythmia recurrence, respectively.

No interim analyses will be conducted in this trial. A *p* < .05 will be considered to indicate statistical significance. A Cox regression analysis will also be utilized for the multivariate analysis regarding the freedom of atrial arrhythmia recurrence. For the secondary endpoints, the AF recurrence‐free rate and AT recurrence‐free rate will be analyzed with the same method as the primary endpoint. The AF burden reduction, total number of ablation sessions, and complication rate will be analyzed between the two groups by an appropriate statistical test according to the type of variables. There are no prespecified subanalyses.

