### Endpoints

2.2

The primary endpoint is designed as the freedom from atrial arrhythmia recurrence such as AF, AT, and atrial flutter (AFL) with or without antiarrhythmic drugs at 18 months after a single procedure. Atrial arrhythmia recurrence is defined as documented AF/AT/AFL lasting more than 30 s after a 90‐day blanking period according to the guidelines.^1^ The safety endpoints include the incidence of procedure‐related major complications such as a stroke, transient ischemic attack, PV stenosis, cardiac tamponade, pericarditis, phrenic nerve injury, major bleeding, vascular access complications (significant groin hematoma, pseudoaneurysm, arteriovenous fistula), atrioesophageal fistulae, gastric hypomotility, heart failure, myocardial infarction, and death according to the guidelines.^1^ To ensure the safety, all adverse events will be reported by the investigators to the coordinating center and reviewed by the institutional review board every month (the members are listed in the Supporting Information: Appendix). In addition, data monitoring will be performed every 6 months by two cardiologists independent of the present study.

The secondary endpoints include the freedom from individual components of the primary outcome (AF, AT, and AFL), atrial arrhythmia freedom after multiple procedures, atrial arrhythmia burden reduction, recurrent arrhythmia types (paroxysmal or persistent), symptomatic atrial arrhythmia recurrence free rate, comparison regarding the atrial arrhythmia freedoms between the radiofrequency group and cryoballoon group in PsAF patients, direct‐current cardioversion free rate, procedure time and fluoroscopy time, success rate of the LAPWI, dimension of the additional isolated area of the LAPW after the LAPWI, freedom from re‐do procedures, durability of the PVI and LAPWI during the second procedure among the patients who underwent a redo procedure, number of repeat procedures, and gastrointestinal symptoms during the periprocedural period. The predictors of atrial arrhythmia recurrence will be also examined among the various factors including the existence of low voltage areas and the kind of devices such as the three‐dimensional mapping systems and ablation catheters.

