### Study patients

3.1

The first patient was enrolled on August 4, 2022, and the enrollment of patients will continue until February 2024. As of August 2023, a total of 331 patients were enrolled. The mean age was 68 ± 9 years old, 270 (81.6%) were men, and 288 (87.0%) patients had persistent AF (Table 2).

**Table 2 clc24164-tbl-0002:** Preliminary data for patients enrolled as of August 2023.

	N = 331
Age, years	68 ± 9
Male gender, *n* (%)	270 (81.6%)
Body mass index	24.7 ± 3.8
PsAF, *n* (%)	288 (87.0%)
Left atrial diameter, mm	41.8 ± 5.9
Left ventricular ejection fraction, %	59.7 ± 10.4

Abbreviation: PsAF, persistent AF.

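### The primary LAPWI comparison is an unadjusted log-rank test although LA diameter and age are recorded at baseline; prespecified adjustment would cost essentially no power and might add about 0 to 7 points

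*Protocol article*

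**What the plan says.** Section 2.7 (Statistical analysis) sets the primary comparison: Kaplan-Meier curves are estimated and "the difference in them between the additional LAPWI group and PVI alone group will be compared based on the" log-rank test. No covariates or strata are attached to that test.

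The same section adds: "A Cox regression analysis will also be utilized for the multivariate analysis regarding the freedom of atrial arrhythmia recurrence". It does not say which covariates enter, whether treatment is one of them, or what role the result plays beside the log-rank test.

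Section 2.2 (Endpoints) describes a related exploratory aim: "The predictors of atrial arrhythmia recurrence will be also examined among the various factors including the existence of low voltage areas", with mapping systems and ablation catheters as further examples.

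Table 2 in section 3.1 lists "Left atrial diameter, mm" at 41.8 ± 5.9 and age at 68 ± 9 years. Section 2.1 stratifies randomization by institution, AF type and PVI device. LA diameter and age are not stratification factors. AF duration enters only through the two-level AF type, with 87.0% of the patients enrolled so far in one level.

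**The concern.** In a time-to-event comparison, leaving out prognostic baseline variables pulls the estimated treatment effect toward the null and lowers power. Adjustment for values already held recovers some of that power without another patient, and it takes chance imbalance in those variables out of the main result.

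A second reason is discretion. The trial is open-label and has no blinded endpoint committee (section 4.1). Section 2.7 plans between-arm tests of baseline characteristics alongside a Cox model whose covariates are not named. An adjusted estimate whose covariates were chosen after imbalances or outcomes had been seen would carry little weight.

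**Working it through.** **Inputs from the article.** The abstract gives the "assumption that 65% and 75% of the PVI and PVI + LAPWI group patients will be free from atrial arrhythmia recurrence". Section 2.6 adds two-sided 5%, 80% power, 516 patients at 1:1, and "we assume the possibility of a 10% dropout of participants". Section 2.7 censors at 18 months. The prognostic strength of LA diameter and age is not given, so it is varied below.

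**1. The plan's own figure.**
- HR = ln 0.75 / ln 0.65 = 0.668.
- Events (Schoenfeld) = 4 × (1.96 + 0.84)² / (ln 0.668)² ≈ 193.
- With censoring at 18 months, the mean event probability is (0.35 + 0.25)/2 = 0.30. Then 193/0.30 ≈ 643, and 643/0.9 ≈ 715, not 516.
- A figure near 516 appears if patients are followed to study end after 18 months of uniform accrual (event probability 0.410): 193/0.410 ≈ 471, and 471/0.9 ≈ 523. A one-sided two-proportion formula with no dropout gives 518. Neither route agrees with the text.

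This is a separate sample-size matter. It is needed here only for the starting power.

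**2. Starting power of the unadjusted test at 18 months.**
- 0.9 × 516 ≈ 464 patients, and 0.30 × 464 ≈ 139 events. Then ½ × √139 × 0.404 − 1.96 ≈ 0.42, which gives power of about 66%.
- With all 516 evaluable there are about 155 events and power is about 71%.

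**3. Gain by formula.** Divide the noncentrality by √(1 − R²). From 80%, the noncentrality is 1.96 + 0.84 = 2.80.
- R² 0.01: +0.4 points
- R² 0.03: +1.2
- R² 0.05: +2.0
- R² 0.10: +4.0
- R² 0.15: +6.0

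From 66%, the gains at the same R² values are +0.4, +1.3, +2.2, +4.6 and +7.0.

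**4. Gain by simulation, log-rank against adjusted Cox.**
- A: 258 per arm, constant hazard from month 3 to 18, 10% dropout spread uniformly, one prognostic score, 3,000 runs (Monte Carlo SE about 0.8 points).
- B: 464 patients, no further dropout, three covariates, 2,500 runs.
- C: as B with 644 patients, where unadjusted power is about 80%.

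Gains in B and C are taken from unrounded figures.

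| Log-hazard SD | AUC / R² | A | B | C (gain) |
|---|---|---|---|---|
| 0 | – | 67.3% and 66.9% (equal within error) | – | – |
| 0.2 | 0.57 / 0.014 | – | 65.4 → 66.0 (+0.6) | −0.1 |
| 0.3 | 0.60 / 0.03 | 67.7 → 68.7 (+1.0) | 66.4 → 67.3 (+0.9) | +0.5 |
| 0.4 | 0.63 / 0.05 | – | 64.8 → 66.8 (+2.0) | +1.4 |
| 0.5 | 0.66 / 0.08 | 69.1 → 72.6 (+3.5) | 65.1 → 68.8 (+3.8) | +2.8 |
| 0.7 | 0.72 / 0.14 | 69.2 → 75.9 (+6.7) | 66.4 → 72.8 (+6.4) | +6.2 |

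A further run with 516 patients, 10% dropout and three covariates showed no visible gain at SD 0.15 to 0.3, about 3 points at 0.5, and 7 to 8 at 0.7.

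**5. What the upper end requires.** If LA diameter and age were independent and equally strong, a combined SD of 0.7 needs 0.7/√2 = 0.495 each, that is HR 1.64 per SD (per 5.9 mm and per 9 years). A combined SD of 0.3 needs 0.212 each, or HR 1.24 per SD.

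**The case against.** The strongest reply is that an unadjusted log-rank test beside Kaplan-Meier curves is a standard and valid analysis of a randomized trial. It inflates no type I error and contradicts nothing else in the article. That stands. A reader might infer that the primary analysis is wrong; the documents do not support this.

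Four further inferences also go too far:

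- *That no adjusted treatment comparison is planned.* Section 2.7 does plan a multivariable Cox model on the same outcome and does not say that treatment is left out. The factors in section 2.2 are examples, not a closed list. The covariates may be named in an analysis plan that is not shown. What can be said is that the Cox model is not the primary comparison.
- *That the trial forgoes a known amount of power.* Every gain above rests on an assumed prognostic strength. The entry limits (LA diameter at most 55 mm, AF at most 3 years) narrow the spread of these variables, and a gain near zero is possible. The simulated models are also correctly specified, which favours adjustment.
- *That continuous AF duration is already held.* Eligibility and AF type need only thresholds, and Table 2 does not list duration. The Discussion notes that symptoms in these patients are often unclear, so onset may be uncertain. AF type already captures part of it.
- *That adjustment would restore the planned power.* At SD 0.7 the adjusted power is still 72.8% to 75.9% in set-ups B and A.

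The objection that a conditional hazard ratio changes what is estimated is also fair. It is a reason to show the unadjusted result alongside, not a reason to forgo adjustment.

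**Conclusion.** The point holds as a matter of efficiency. The stated primary comparison uses no covariates although LA diameter and age are available for every patient assessed for entry. Prespecified adjustment would be expected to cost essentially no power and could add about 0 to 7 points. This rests on the planning rates, proportional hazards, censoring at 18 months, and a combined log-hazard SD between 0 and 0.7, which is assumed. Below an SD of about 0.3 the gain is at most about 1 point and hard to tell from simulation error. The shortfall against 80% (about 9 to 14 points at 18 months) comes from the sample size and remains a separate problem.

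**What to change.** Before database lock, and without reference to unblinded outcome data, amend section 2.7 as follows:

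- Test the LAPWI effect (two-sided 5%) as the treatment coefficient in a Cox model with prespecified pre-randomization covariates: LA diameter (mm) and age. Add AF duration only if it is captured as a continuous value.
- Include the randomization factors AF type and PVI device, or stratify on them. Figure 1 combines these into three groups. Say also how institution is handled.
- Report the Kaplan-Meier curves and the log-rank test beside the adjusted result.
- Keep low voltage area, mapping system and ablation catheter out of this model. The voltage map is made after PVI and only if sinus rhythm can be maintained. In cryoballoon patients, radiofrequency use is tied to the arm, because LAPWI requires it. Nothing says that the mapping system is fixed before randomization.
- Give a simple rule for missing baseline covariates, such as mean imputation, so that no randomized patient is dropped. Section 2.7 rules out imputation next to the baseline comparisons, so this needs explicit wording.

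The cost is one paragraph and one model. The hazard ratio becomes conditional on the covariates. Because enrolment is under way (331 of 516 by August 2023), the change must be documented as an amendment with its date and reason.

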On the other hand, triggers other than the PVs (non‐PV triggers), which initiate AF, have been focused on as a strategy for AF ablation. It has been reported that non‐PV triggers are identified in ~10% of PsAF/long‐PsAF patients.^8^ In another investigation, sufficient clinical outcomes could be obtained in those with treatable non‐PV triggers as compared with those with persistent triggers after ablation for non‐PV triggers such as including a superior vena cava (SVC) isolation or LAPWI.^9^ According to the expert consensus statement, it is recommended to consider ablation of reproducible focal triggers identified outside the PV ostia (Class Ⅱa), which is more strongly recommended than an LAPWI (Class Ⅱb).^10^ However, this ablation strategy was not adopted in most of the trials in which the efficacy of an additional LAPWI was examined. Therefore, there is a value in evaluating the true efficacy of an additional empirical LAPWI after a conceivable best practice of AF ablation including a non‐PV trigger ablation in addition to the PVI in PsAF/long‐PsAF patients.

With regard to the safety, possible gastroesophageal complications need to be considered, especially when an LAPWI is added because the PV component is closely adjacent to the esophagus and periesophageal vagal nerve branches. There are some investigations of esophageal thermal injury including cases in which linear ablation of the roof or floor of the LA was performed, but they showed that linear ablation was not associated with increasing esophageal injuries.^11^, ^12^ Some observational studies reported that the prevalence of gastric hypomotility detected on gastroesophageal endoscopy, which is attributed to the periesophageal vagal nerve injury, was significantly higher in cases with an additional LAPWI as compared to those with a PVI alone.^13^, ^14^ Further investigations regarding the safety after an additional LAPWI are required.

The incidence of iatrogenic atrial tachycardia (AT) after the procedure would be a potential disadvantage of an adjunctive LAPWI. According to the meta‐analysis of LAPWIs, the prevalence of an AT recurrence tends to be higher after an additional LAPWI than after a PVI alone.^4^ In addition, there has been a report that demonstrated that peri‐mitral ATs were the main cause of recurrent ATs^15^ after an LAPWI. The influence of an additional LAPWI should be investigated further.

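### Section 2.2 lists atrial arrhythmia burden as the endpoint but Section 2.7 analyses AF burden; read literally, AF replaced by AT or AFL could pass as a burden benefit of LAPWI

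*Protocol article*

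**What the plan says.** Section 2.2 (Endpoints) lists "atrial arrhythmia burden reduction" among the secondary endpoints. The same section counts AF, AT and AFL alike as recurrence in the primary endpoint, and names the three as separate components in another secondary endpoint.

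Section 2.7 (Statistical analysis) gives the matching analysis as: "The AF burden reduction, total number of ablation sessions, and complication rate will be analyzed between the two groups", to be done "by an appropriate statistical test according to the type of variables". The sentence just before it treats AF recurrence-free rate and AT recurrence-free rate as two separate outcomes.

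The article does not define burden, and it does not say from what value a reduction is measured. Under Section 2.5 (Postablation management), the routine 7-day Holters "will be performed at 6, 12, and 18 months after the procedure".

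On AT, the Introduction reports from a meta-analysis that "the prevalence of an AT recurrence tends to be higher after an additional LAPWI than after a PVI alone", and it treats iatrogenic AT as a possible drawback of the added lesion set. The Discussion mentions that risk again.

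**The concern.** The endpoint listed and the quantity to be analysed are different variables. They differ only in time spent in AT or AFL, and that is where the article leads one to expect the arms to differ. If posterior wall isolation turns some AF into AT, AF burden falls although the patient spends just as long in arrhythmia. An AF-only analysis would record that as improvement, and the error would favour LAPWI.

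The analysis would also depart from the trial's own idea of success, since an AT episode after the blanking period is a failure in the primary endpoint. Anyone following Section 2.7 to the letter would not be analysing the endpoint listed in Section 2.2.

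**Working it through.** **Step 1: the passages side by side.**

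- Section 2.2, burden endpoint: all atrial arrhythmia.
- Section 2.7, burden analysis: AF.
- Section 2.2, primary endpoint: AF, AT and AFL all count.
- Section 2.7, preceding sentence: AF and AT kept apart as distinct outcomes.

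The article generally uses AF as one member of the set AF/AT/AFL. The literal reading of the Section 2.7 burden item is therefore AF only.

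**Step 2: the size of the error in general terms.** Write AF and AT for mean post-procedure burden as percent of recorded time, with AFL included in AT.

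- AF-only difference = AF(PVI) − AF(LAPWI)
- Total difference = [AF(PVI) + AT(PVI)] − [AF(LAPWI) + AT(LAPWI)]
- AF-only difference minus total difference = AT(LAPWI) − AT(PVI)

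The apparent benefit is overstated by exactly the excess AT/AFL burden in the LAPWI arm, and by nothing if the two arms have equal AT/AFL burden.

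**Step 3: illustration.** The article gives no burden mean, spread or target effect, so there is no figure to reproduce. Every value below is an assumption, chosen only to show the range of behaviour.

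| Assumed case | PVI: AF / AT | LAPWI: AF / AT | AF-only difference | Total difference | Overstatement |
|---|---|---|---|---|---|
| 5 points of AF become AT | 10 / 2 | 5 / 7 | 10 − 5 = 5 | 12 − 12 = 0 | 7 − 2 = 5 |
| 3 points of AF become AT | 10 / 2 | 7 / 5 | 10 − 7 = 3 | 12 − 12 = 0 | 5 − 2 = 3 |
| One third of a 6% burden becomes AT, none in controls | 6 / 0 | 4 / 2 | 6 − 4 = 2 | 6 − 6 = 0 | 2 − 0 = 2 |
| No exchange, AF truly lower | 10 / 2 | 8 / 2 | 10 − 8 = 2 | 12 − 10 = 2 | 2 − 2 = 0 |

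In the first three cases the AF-only measure shows a benefit that the listed endpoint does not. In the last, the two agree.

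**Step 4: the reference for a reduction.** Section 2.5 gives some assessments an explicit time before the procedure. Echocardiography, for example, is done "before the procedure and at 12 months after the procedure to assess the atrial remodeling and cardiac function"; CT (where the patient consents) and the gastrointestinal questionnaire are also timed before the procedure. No such time is given for the Holter, and no assumed starting value is stated. The flow chart (Figure 3) is not shown. The text therefore leaves the reference open but does not show that there is none.

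**The case against.** The best defence is that Section 2.7 paraphrases. The same sentence turns the number of repeat procedures into a total number of ablation sessions, and procedure-related major complications into a complication rate. AF burden may likewise be shorthand for the listed endpoint, and nothing in the article says that AT time will be scored as arrhythmia-free. This stands in part: an AF-only analysis is the literal reading, not an established intention. But the preceding sentence separates AF from AT, which weakens the shorthand explanation, and if it is shorthand the wording still needs correcting.

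The second defence is that AT is not hidden. It counts in the primary endpoint and has its own recurrence-free analysis. This also stands, and it confines the problem to one secondary endpoint. It does not remove it, because those analyses concern time to recurrence and would not correct a burden result that leaves out AT time.

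Several stronger readings are tempting but not supported:

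- *The trial has no baseline Holter.* The article is condensed and Figure 3 is not shown, so this cannot be concluded.
- *Baseline burden cannot be taken as continuous AF.* Section 2.3 asks only for an episode of more than 7 days in the preceding year. But Section 2.1 excludes paroxysmal AF and defines AF duration by its persistence, so a near-continuous baseline is a plausible reading. The article does not say which reference applies.
- *The missing baseline is what lets AT count as benefit.* These are separate matters; the AT problem follows from the AF-only wording alone.
- *A false one-third reduction (4% against 6%) is to be expected.* That case is assumed throughout, and no AT at all in controls is an extreme choice.
- *Not naming the test is an error.* For a secondary endpoint in an article, that is ordinarily left to the analysis plan.

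**Conclusion.** The mismatch between Sections 2.2 and 2.7 is real and should be corrected. Taken as written, Section 2.7 omits AT and AFL time from the burden comparison, and any resulting bias would favour LAPWI if AT is more frequent in that arm, as the Introduction suggests. Its size is unknown: it equals the excess AT/AFL burden under LAPWI, which the documents do not allow one to estimate and which may be zero.

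The conclusion rests on two conditions: that AF burden means AF only, and that some AF is replaced by AT or AFL more often after LAPWI than after PVI alone. It concerns one secondary endpoint and does not touch the primary analysis. The lack of a stated reference for a reduction is a lesser point of clarification.

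**What to change.** In Section 2.7, replace AF burden with total AF+AT+AFL burden, defined as percent of recorded time on the scheduled 7-day Holters at 6, 12 and 18 months, and make this the analysis of the endpoint listed in Section 2.2. Report AF burden and AT/AFL burden separately by arm, as description, so that any exchange of one for the other can be seen.

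State the reference for the reduction. If a pre-procedure recording exists, name it; if not, compare the post-procedure burden level between the arms and rename the endpoint to match.

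The cost is a few words in Sections 2.2 and 2.7. The recordings are the same, and neither the sample size nor the primary analysis changes. The article describes enrolment as still open and plans no interim analysis, so at that stage the wording could be settled before any planned comparison of outcomes.
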